### Secondary endpoints

Secondary endpoints include each element of the composite primary endpoint to investigate dose-related toxicities, as well as serum DON levels used to calculate PK parameters of the drug. Additional secondary endpoints for all participants include PK parameters such as volume of distribution, maximum concentration (*C*_max_), time to maximum concentration (*T*_max_), area under the curve (AUC), clearance, elimination rate constant, and terminal half-life (*T*_½_). Non-compartmental analysis is used for the estimation of PK parameters.

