Similarly, pediatric participants who fulfill enrollment criteria have pre-DON laboratory studies for safety and DON levels (Fig. 1B). Next, an IV line is placed, and participants receive IV fluids at standard maintenance rates. At enrollment, a lumbar puncture (LP) is performed both to rule out bacterial CNS co-infection and for DON mechanistic studies. IV artesunate is administered immediately upon confirmation of a CM diagnosis. Participants undergo a brain MRI (if available), TCD, and at least 30 min of EEG recording before administration of DON (or placebo). Participants remain hospitalized for a minimum of 24 h. Each pediatric participant is pre-medicated with ondansetron (0.15 mg/kg up to 5.0 mg) and receives DON IV or placebo at the pre-specified dose 30 min later. Ondansetron dosing is repeated at 8 and 16 h after DON administration. Due to the precariousness of CM and the young age of the pediatric participants, PK studies are employed through sparse sampling techniques at three of the following time points: 10 min, 30 min, 60 min, 90 min, and 3 h, 6 h, 12 h, and 18 h post-DON. A population PK analysis is used to estimate PK parameters in children. A repeat LP is performed 4 h after DON or placebo administration for metabolic studies. Participants remain hospitalized until their BCS is ≥ 3, they can drink unaided, and can sit with minimum assistance. Seven and 14 days after DON administration, blood samples for safety are obtained. At 1 and 6 months post-admission, surviving pediatric participants are examined for neurological sequelae and assigned a Glasgow Outcome Score (GOS-E) category.

Should any AEs or SAEs occur, they will be followed until resolution. During the 6-month enrollment period, should participants develop any clinical symptoms of concern, they are encouraged to return to visit study personnel for evaluation.

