## Statistical methods

### Statistical methods for primary and secondary outcomes {20a}

The primary analysis is the comparison of the active doses against placebo in pediatric participants. For the dichotomous safety endpoints, unadjusted pairwise analyses use 95% confidence intervals of the difference in proportions between dose groups using Wilson score criteria. For the exploratory efficacy endpoints of cEEG amplitude or frequency, MRI brain volume score, age and sex standardized mean, and diastolic flow pattern for TCD, unadjusted pairwise analyses will calculate the 95% confidence interval of the mean difference of each endpoint’s first post-treatment measurement between dose groups using a *t*-statistic.

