### Interim analyses {21b}

After 50% of pediatric participants are enrolled, an interim analysis will assess the benefit-risk of the study drug to inform whether the study should continue. If a decision is made to continue, the dose–response relationship for both the primary safety endpoint and exploratory efficacy endpoints will inform which doses to study in the second half of pediatric enrollments.

For the exploratory efficacy endpoints of EEG amplitude or frequency, MRI brain volume score, and flow velocity on TCD, we will compare different dose groups using Welch’s *t*-test. We may use a linear regression dose response model to predict the effect size compared to placebo as a function of dose. For each exploratory efficacy outcome measured after DON administration, response may be modeled by dose group, or a more complicated model may be used such as a logit of area under the curve of the exposure profile, adjusting for disease severity at baseline.

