### Methods for additional analyses (e.g., subgroup analyses) {20b}

Exploratory analyses will compare DON doses to each other to assess preliminary efficacy. We will explore the impact of covariates including age, sex, and other characteristics (admission BCS, MRI brain volume score, serum glucose, serum lactate, cEEG, and/or admission TCD phenotype) by multivariable regression on the exploratory outcomes. In this multivariable model, dose will be either a categorical variable with fixed doses as categories or will account for PK of exposure measurements by using the area under the curve or *C*_max_ in the logistic regression. This adjusted model will only include characteristics that predict outcomes as determined by bivariate analyses.

For MRI brain volume scoring, GOS-E scoring, and TCD phenotype, which all rely on physician scoring, we will report Cohen’s Kappa measure on inter-rater reliability for outcomes evaluated by more than one physician. For endpoints measured multiple times during follow-up, sensitivity analyses will explore variation of these measurements over time in different groups by including random effects for time of measurement in the multivariable regression models.

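### Some exploratory and secondary analyses are stated with methods that do not fit their data or that conflict between sections; the clearest cases are logistic regression for continuous markers and a mean difference for a TCD flow pattern

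*Protocol article*

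**What the plan says.** All references are to the protocol article.

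- **Adjusted model, {20b}.** Covariates are explored "by multivariable regression on the exploratory outcomes". Dose enters as categories, or the model "will account for PK of exposure measurements by using the area under the curve" or the maximum concentration, and the sentence ends by naming the model a logistic regression.
- **Unadjusted comparison, {20a}.** The list of exploratory endpoints ends with "diastolic flow pattern for TCD, unadjusted pairwise analyses will calculate the 95% confidence interval of the mean difference", based on a t-statistic and each endpoint's first post-treatment value.
- **Interim analysis, {21b}.** The TCD measure is flow velocity, compared by Welch's t-test. Linear dose-response regression is optional. So is this: "a more complicated model may be used such as a logit of area under the curve of the exposure profile".
- **Repeated measurements, {20b}.** For endpoints measured several times, the stated aim is that "sensitivity analyses will explore variation of these measurements over time in different groups". The method named for this purpose is "including random effects for time of measurement in the multivariable regression models".
- **PK.** Under Secondary endpoints, PK parameters are listed for all participants, and then: "Non-compartmental analysis is used for the estimation of PK parameters". Participant timeline {13} says that in children "PK studies are employed through sparse sampling techniques at three of the following time points", and assigns a population PK analysis to them.

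**The concern.** A logistic model needs a binary or categorical outcome, and a mean difference needs a numerical one. Where the article attaches these methods to the other kind of outcome, the analysis cannot be run as written, and the analyst must choose a replacement with data in hand. This matters somewhat more than usual for exploratory endpoints, because {21b} lets the exploratory efficacy dose-response inform which doses are studied in the second half of pediatric enrollment.

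The random-effects sentence raises a different issue. EEG is measured at three post-dose times and TCD at two, in the same child. A model whose only random factor is time would treat these values as independent between times and would attach wrong standard errors to group comparisons.

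**Working it through.** **The plan's own figure first.** With exact 90% central intervals and a true rate of 20%, the Sample size section claims over 85% power to exclude serious adverse event rates above 54%, 46% and 37%.

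| On DON | Largest qualifying count | Upper limit | Power |
|---|---|---|---|
| 14 | 4 | 54.0% | 87.0% |
| 28 | 8 | 45.7% | 91.0% |
| 56 | 14 | 36.3% | 86.4% |

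The claim reproduces, and nothing below bears on it.

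**(a) Logistic regression.** The Sample size section calls the exploratory endpoints continuous. {21b} analyses EEG amplitude or frequency, brain volume score and flow velocity by comparing means. {20b} introduces regression on these same outcomes and then names it logistic. No dichotomization is stated anywhere in the article. The sections cannot all be followed for the continuous markers.

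**(b) TCD.** The exploratory endpoints list phenotype and flow velocities as separate measures. {20a} lists an age- and sex-standardized mean and, as a further item, the diastolic flow pattern. {20b} includes phenotype among the physician-scored measures checked with Cohen's kappa. Kappa alone does not settle the type, since the brain volume score is also on that list. The word pattern, set beside a separately listed mean, does point to a category, for which a t-based mean difference has no meaning. The TCD endpoint also differs between {20a} (pattern) and {21b} (velocity).

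**(c) Random effects, read literally.** Let m be the number of post-dose values per child (3 for EEG, 2 for TCD) and ρ the within-child correlation. The article gives no ρ, so 0.3 to 0.7 is assumed.

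For a group difference averaged over time, the true variance exceeds the one assumed under independence by the design effect DE = 1 + (m − 1)ρ. The large-sample type I error is 2 × [1 − Φ(1.96/√DE)].

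| m | ρ | DE | 1.96/√DE | Type I error |
|---|---|---|---|---|
| 2 | 0.3 | 1.3 | 1.719 | 8.6% |
| 2 | 0.5 | 1.5 | 1.600 | 11.0% |
| 2 | 0.7 | 1.7 | 1.503 | 13.3% |
| 3 | 0.3 | 1.6 | 1.550 | 12.1% |
| 3 | 0.5 | 2.0 | 1.386 | 16.6% |
| 3 | 0.7 | 2.4 | 1.265 | 20.6% |

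Simulation without a treatment effect, at 14 v 8, 28 v 8 and 56 v 16 children, agrees to within one percentage point. When the child is respected, the error is 4.6–5.2%.

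For a change between two times compared across groups, the true variance is smaller than assumed, by the factor 1 − ρ. The error is 2 × [1 − Φ(1.96/√(1 − ρ))]:

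- ρ = 0.3: 1.96/√0.7 = 2.343, giving 1.9%
- ρ = 0.5: 1.96/√0.5 = 2.772, giving 0.6%
- ρ = 0.7: 1.96/√0.3 = 3.578, giving 0.04%

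So the same omission makes one kind of test too liberal and the other too conservative.

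**(d) PK.** Adults have eight post-dose samples, for which non-compartmental analysis is workable. Children have three of the same eight time points, and {13} gives them population PK. The only defect is that the non-compartmental sentence under Secondary endpoints names no population and follows a list for all participants.

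**(e) Logit of AUC.** logit(x) = log[x/(1 − x)] exists only for 0 < x < 1. A child on placebo has an AUC of 0, and an AUC on DON has no upper bound of 1.

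**The case against.** Most of this is loose wording in a condensed article, about exploratory or secondary analyses.

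- A logistic-family model can suit TCD phenotype, which is among the exploratory endpoints. That is true, but it does not explain the label for the continuous markers.
- Pattern may be a slip for diastolic velocity, since {21b} names velocity. If so, the repair is one word, but it still has to be made.
- Random effects for time may be shorthand for time effects within each child, and covariance structure is usually left to the analysis plan. This stands: the article neither names nor excludes a participant effect.
- The stated purpose of that model is variation over time by group. For that question the literal model is conservative, so it would be wrong to say in general that its standard errors are too small.
- The logit of AUC is one optional example beside usable alternatives. This also stands.

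A reader might infer that the trial plans non-compartmental PK from three samples per child. The article does not support that, because {13} assigns population PK to children in the same paragraph as the sparse sampling.

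A reader might also infer that the main comparisons have wrong error bars. They do not: {20a} uses one post-treatment value per child, {21b} uses Welch's test for continuous markers, and safety uses Wilson intervals.

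**Conclusion.** The point holds in a limited form. Items (a) and (b) stand on the text alone: each attaches a method to an outcome it does not fit, and each conflicts with another section. Item (d) is an inconsistency to reconcile, and item (e) an optional term that cannot be computed as written.

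Item (c) holds only on the literal reading. Its size there, about 9–21% for a time-averaged contrast and about 2% or less for group-by-time contrasts, rests on assumed correlations of 0.3–0.7 that are equal between all times. It reaches one sensitivity analysis of exploratory endpoints and should not be the headline.

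The Wilson safety intervals, the Welch t-tests and the stated power figures are not affected.

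**What to change.** - **{20b}, adjusted model:** state linear regression for EEG amplitude and frequency, flow velocity and brain volume score. Keep logistic or proportional-odds models for categorical outcomes such as TCD phenotype.
- **{20a} and {21b}, TCD:** name the same TCD endpoint in both. Use the mean difference for flow velocity, and an exact or ordinal method for pattern or phenotype.
- **{20b}, repeated measures:** state a participant random effect or an unstructured within-child covariance, with categorical time, treatment and treatment-by-time as fixed effects.
- **Secondary endpoints:** limit the non-compartmental sentence to adults and refer to the population PK analysis for children.
- **{21b}, exposure:** replace the logit of AUC with a defined term that allows zero exposure on placebo, for example an Emax term.

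The cost is wording in the protocol and analysis plan. No data collection, sample size or safety analysis changes. The wording should be settled before the interim analysis, because the exploratory results inform cohort 4.

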### Methods in analysis to adjust for protocol non-adherence and statistical methods to adjust for missing data {20c}

In both adult and pediatric studies, the primary population for analyses of all endpoints is all intent to treat (ITT) participants. Every effort will be made to minimize protocol deviations and minimize missing values. If there are deviations from protocol where treatment received differs from the treatment to which the participant is randomized, the primary analysis population will be “as-treated.” Because the primary goal is to determine dose safety, when dose randomized differs from dose received, we will analyze outcomes by the dose received and conduct sensitivity analyses on the ITT population with “as-randomized” assignment. To adjust for missing values in our analyses, we may use multiple imputation methods to measure dose effect while accounting for uncertainty arising from the missing value(s). We will generate 25 imputed datasets and fit the multivariate models accounting for model uncertainty as well as uncertainty from imputation.

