## Introduction

### Background and rationale {6a}

Cerebral malaria (CM), defined as an otherwise unexplained coma in someone with *Plasmodium falciparum (Pf)* parasitemia, is the most lethal form of severe malaria [1, 2]. Ninety percent of CM mortality occurs in children, the vast majority of whom are less than 5 years old [3]. Despite treatment with the highly effective anti-malarial, intravenous (IV) artesunate, mortality rates are 15–25%, and children who survive often suffer severe neurological sequalae. At present, there are no predictive diagnostics for which children with malaria will develop CM nor therapy for CM after children progress to severe disease. Thus, the public health burden is enormous.

Current knowledge of the cellular and molecular mechanisms that underlie CM disease pathology are incomplete. The observation of heavily infected red blood cell (iRBC) sequestration in the cerebral vasculature of children who died of CM, often accompanied by intra- and peri-vascular pathology including ring hemorrhages, led to the generally accepted hypothesis that iRBC sequestration in the cerebral vasculature and the resulting mechanical obstruction lead to inflammation, impaired vasoregulation, and blood brain barrier (BBB) dysfunction thus causing this severe progression of malaria [4]. Therapies targeting the purposed downstream effects of sequestration were investigated in multiple clinical trials [5–19], but none improved clinical outcomes. These failures suggested that the downstream effects of iRBC sequestration were poor targets of therapies.

Studies in the mouse model of CM (referred to as experimental cerebral malaria or ECM) provided strong evidence for the role of parasite specific CD8^+^ T cells in the pathology of CM [20]. CD8^+^ T cells had not been targeted for CM therapy in humans, in part, because they had not been reported in the cerebral vasculature of children who died of CM [21, 22]. We recently provided definitive evidence for the presence of CD8^+^ T cells lining the cerebral vasculature in children who died from CM [23]. Our findings point to a mechanism by which CD8^+^ T cells function in disease pathophysiology based on the extraordinary similarities in the distribution of CD8^+^ T cells in the brains of children with CM and in mice with ECM. These observations open new avenues for treatment of CM that involve modulating CD8^+^ T cells with the wealth of available T cell targeting therapeutics.

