### Objectives {7}

The primary objective of this study is to evaluate the safety of a single IV dose of DON in healthy adults, adults with uncomplicated malaria, and children 6 months to 14 years old with World Health Organization (WHO) defined CM. Our secondary objective is to determine the PK profile of a single dose of DON administered to an individual at one of four doses studied. Our exploratory objectives are to both determine the preliminary efficacy of DON and to explore the metabolic mechanism(s) of action of DON in children with CM. We hypothesize that a single dose of DON will be safe and tolerable in healthy adults, adults with uncomplicated malaria, and children with CM over the studied dose ranges. We evaluate increasing doses of DON using preliminary markers of efficacy in children with CM, namely changes in patterns on continuous electroencephalography (cEEG), improved MRI brain volume scores, and improved flow velocities on transcranial doppler (TCD) all of which have been previously established as prognostic biomarkers associated with CM mortality [26, 41, 42].

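### Post-dose markers are compared as means with no separate handling of death before measurement, so the 24 h MRI comparison becomes one among survivors

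*Protocol article*

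**What the plan says.** **Analysis.** Statistical methods {20a} summarises the EEG, MRI and TCD markers by the "95% confidence interval of the mean difference of each endpoint’s first post-treatment measurement between dose groups", based on a t-statistic. For the interim, Interim analyses {21b} states: "we will compare different dose groups using Welch’s *t*-test". It adds that dose-response regression, or a model adjusting for baseline severity, may be used.

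**Use.** The same section says that "the dose–response relationship for both the primary safety endpoint and exploratory efficacy endpoints will inform which doses to study" in the second half of pediatric enrolment.

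**Absent values.** Section {20c} makes the intention-to-treat participants the primary population for all endpoints, with analysis by dose received where that differs. Its only tool for absent values is optional: "To adjust for missing values in our analyses, we may use multiple imputation methods to measure dose effect". It continues: "We will generate 25 imputed datasets and fit the multivariate models". Death is not mentioned there.

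**Disease.** Background {6a} reports that "mortality rates are 15–25%, and children who survive often suffer severe neurological sequalae". Objectives {7} describes the three markers as "previously established as prognostic biomarkers associated with CM mortality".

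**Timing.** Under Exploratory endpoints, MRI has one post-dose value, at 24 h. EEG samples are taken at 3, 6 and 12 h, and TCD at 4 and 24 h. Electrographic seizures are totalled in minutes over the first 12 h.

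**The concern.** A child who dies before the 24 h scan has no post-dose brain volume score. Under the stated methods that child either drops out of the t-based comparison or, in the multivariable models, may be given an imputed value. The text provides no third route.

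The markers predict death, so the scores lost this way would be expected to be among the worst. If a dose keeps very sick children alive until the scan, their poor scores enter that arm's mean, while the matching placebo children are absent from theirs. The survivors' means can then move against the better dose.

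The seizure total has a related fault. A child who dies at 3 h can contribute at most 180 of the 720 minutes in the window, so an early death lowers the count and looks like benefit.

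The practical stake is the interim review, where the marker results help to choose the doses for cohort 4.

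**Working it through.** **1. The plan's own figures.** The article gives no numerical power for the markers, so there is no stated figure to reproduce on this point. Its safety power figures do reproduce, using a one-sided 95% exact upper limit and a true rate of 20%:

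- N = 14: up to 4 events, limit 54.0%, power 87.0%.
- N = 28: up to 8 events, limit 45.7%, power 91.0%.
- N = 56: up to 14 events, limit 36.3%, power 86.4%.

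The safety side is therefore not in question.

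**2. Expected deaths at the interim if DON has no effect.** Sample size {14} gives 36 children: 8 on placebo and 28 on DON, which is 14 per dose.

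- All: 36 × 0.15 = 5.4 to 36 × 0.25 = 9.0.
- Placebo: 8 × 0.15 = 1.2 to 8 × 0.25 = 2.0.
- Each dose: 14 × 0.15 = 2.1 to 14 × 0.25 = 3.5.

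The share that falls before 24 h is not in the document.

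**3. The mechanism by hand.** Assume that higher is worse, that children who would survive anyway average 5, that rescued children average 7, and that all deaths precede the scan. These scores are illustrative.

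- Early death 15% v 5%: DON mean = (0.85 × 5 + 0.10 × 7) / 0.95 = 5.21, against 5.00 on placebo.
- Early death 25% v 12.5%: DON mean = (0.75 × 5 + 0.125 × 7) / 0.875 = 5.29, against 5.00.

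Now rank death as worst, and let every rescued child score below every child who would survive anyway. In the first case, the probability that a DON child does better (ties count half) is 0.85 × 0.15 + 0.5 × 0.85² + 0.10 × 0.15 + 0.5 × 0.05 × 0.15 = 0.507. The same sum gives 0.516 in the second case. The direction is restored, though only slightly.

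**4. Range of the shift.** This is a simulation with 300,000 children per arm. Assumptions not in the document: marker SD 1, correlation 0.7 with baseline severity, logistic death risk rising with severity, DON mortality 5–10%, and 25%, 50% or 100% of deaths before the scan. DON is given no effect on the marker itself.

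| Mortality, placebo v DON | Survivors' mean difference in SD (+ is against DON), at 25 / 50 / 100% early | P(DON better), death ranked worst |
|---|---|---|
| 15% v 10% | 0.01 / 0.02 / 0.05 | 0.51 / 0.51 / 0.51 |
| 15% v 5% | 0.03 / 0.05 / 0.09 | 0.50 / 0.51 / 0.53 |
| 20% v 10% | 0.02 / 0.05 / 0.08 | 0.51 / 0.51 / 0.53 |
| 20% v 5% | 0.04 / 0.07 / 0.13 | 0.51 / 0.52 / 0.55 |
| 25% v 10% | 0.03 / 0.07 / 0.13 | 0.51 / 0.52 / 0.55 |
| 25% v 5% | 0.05 / 0.09 / 0.17 | 0.51 / 0.53 / 0.56 |

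- Imputation from correctly modelled baseline severity brings the difference to about 0 (−0.005 to +0.005). It removes the adverse shift but gives no credit for survival.
- With a true marker benefit of 0.2 SD, the survivors' difference shrinks to between −0.18 and −0.03 SD. The sign does not reverse.

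**5. Scale.** For one dose against pooled placebo at the interim, the standard error is √(1/14 + 1/8) = 0.44 SD, and the effect detectable with 80% power is about 1.3 SD. The largest shift is 0.17 / 0.44 = 0.39 standard errors. It does not shrink with enrolment: at 56 v 16 the standard error is √(1/56 + 1/16) = 0.28 SD.

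**The case against.** The strongest reply is that this is an article condensing a fuller protocol, and that a rule for deaths may stand in that protocol or in the analysis plan. Silence alone would not be a point. What remains is that the article has a missing-data section, names its methods and fixes comparisons of means. Followed as written, these give a survivor-selected MRI comparison.

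Several stronger readings are tempting, and the document does not support them:

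- **That dead children's scores will be imputed.** Section {20c} speaks only of missing values, says that imputation may be used, and links the imputed datasets to the multivariate models. It does not link them to the interim Welch test. Values can also be missing because no scanner was available.
- **That all three markers are equally affected.** The primary comparison uses the first post-treatment value, which is at 3 h for EEG and 4 h for TCD. Few deaths would be expected by then, although the document does not give their timing. MRI is the exposed marker.
- **That the interim test uses seizure minutes.** They are listed as an exploratory endpoint but are not named for the t-interval or the Welch test.
- **That a survival benefit, or a lethal dose, would go unseen.** Deaths count in the 14-day SAE endpoint, which {21b} also uses for the dose choice. They also feed the halting rules, and the DSMB sees unblinded SAEs. Even so, an any-SAE endpoint weighs a death like any other SAE and does not repair the marker comparison.

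The planned baseline-adjusted models reduce imbalance in severity. They do not by themselves define an outcome for a child who died.

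**Conclusion.** The point holds for the 24 h MRI score and, as a matter of endpoint definition, for the 12 h seizure total. It applies only weakly to the first EEG and TCD values. The plan does not separate death before measurement from other missing data, and its mean comparisons then describe survivors.

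The shift against a life-saving dose is about 0.01 to 0.17 SD under the assumptions in the working. The upper end needs 25% v 5% mortality with every death before the scan. That is well below the interim standard error of 0.44 SD, so a reader should not infer that the interim dose choice would be reversed. The shift is nevertheless systematic and is cheap to avoid. Severity is low to moderate, because these endpoints are exploratory and deaths are counted on the safety side.

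**What to change.** In {20a}, {20c} and {21b}, state how death before a scheduled measurement is handled:

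- For the 24 h MRI score, and for any later EEG or TCD value that is analysed, add a between-group comparison that ranks death before the measurement as worst. Keep the mean difference among survivors as descriptive.
- Limit multiple imputation to children who were alive but not measured, for example because MRI was not available.
- Report seizures as minutes per recorded hour, with death before 12 h ranked worst.
- At the interim, show the number of deaths before each measurement by arm, beside the marker results.

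This changes wording and programming only and needs no new data. The cost is that the effect is no longer a simple mean difference and is harder to put in clinical units, which is why the survivors' mean difference should stay in the report.
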